#### Secondary Outcome Measures

The secondary outcome measures are the mean change in the nasal endoscopy index (assessment of nasal membrane color, pale or hyperemia; rhinorrhea, watery or yellow; and inferior turbinate swelling, hypertrophy) and the mean change in laboratory tests at baseline and on day 45.

The nasal endoscopy index will be evaluated using the assessment method by Kim et al [20]. The doctor assesses the nasal membrane and inferior turbinate of the patient via nasal endoscopy. When evaluating the nasal membrane color, either the score for paleness or hyperemia must be 0 (eg, if the pale score is 2, the hyperemia score should be 0; if the nasal membrane color is normal, both pale and hyperemia scores are 0). The same rule is applied in the case of the rhinorrhea score. If there is no rhinorrhea, the scores for wateriness and yellowness are 0, and the yellow score is measured by evaluating the rhinorrhea parameter. An inferior turbinate swelling score is used to evaluate the nasal obstruction (Multimedia Appendix 2).

### Timelines With Deliverables

The total study period is 24 months and divided into 3 cycles (ie, 1-3.5 months for the treatment and standard trial drugs) along with the procurement of the certificate of analysis and finalization of the laboratory tests. Staff recruitment, purchases of equipment and other logistics, finalization of case report forms (CRFs), etc, were also done during this period. The timeline for participant recruitment will be 15 months, the treatment period will be 1.5 months, and the follow-up period will be 3 months. Data compilation, analysis, report preparation, and publication will be done during the last month.

### Sample Size

In a previous pilot study on this Ayurvedic intervention, a change of 14 points in the CARAT score was observed. For this study, it was assumed that a change of 10 points would be seen in the placebo group. With an SD of 6 points based on the results of the previous pilot study, a sample size of 35 participants per group was calculated to provide 80% power, with a 95% CI.

Assuming a dropout rate of 20%, a total of 90 participants, 45 per group, will be included in this trial.

n_1_ = n_2_ = 2 *σ*^2^ [(Z_1 – α/2_) + (Z_β_)]^2^ ÷ Δ^2^

n_1_ = n_2_ = 2 * (6)^2^ [(1.96 + 0.84)]^2^ ÷ (4)^2^

n_1_ = n_2_ = 35

where Δ is |μ_2_ – μ_1_| (the absolute difference between two means), σ is the variance of two means, n_1_ is the sample size for group 1, n_2_ is the sample size for group 2, α is the probability of type 1 error (usually .05), β is the probability of type 2 error (usually .2), and z is the critical *Z* value for a given α or β.

### Randomization and Allocation

A randomization chart has been generated with the help of computer-generated random numbers. Participants will be randomized in a ratio of 1:1 to either the study group or the control group. The randomization schedule will be strictly controlled and remain with the biostatistician/data analyst. Sequentially numbered, sealed, opaque envelopes will be used to conceal the allocation.

### Study Procedure

The participant will be screened for AR as per the inclusion criteria. Prior to any trial-related activity, the investigator will give the participants or their parents or guardians information about the trial verbally and in printed form. The investigator will ensure that the participant is fully informed about the aims, procedures, discomforts, and expected benefits of the trial. It must be emphasized that participation is voluntary, and participants have the right to discontinue the trial at any time without any prejudice.

After the screening, suitable participants will be enrolled in the study after signing the consent form. The required tests will be carried out. Within 1 week or as soon as the laboratory results are received and found to be within the eligibility limits, the participant will be enrolled in the study, with this day being recorded as visit 1 or the baseline visit. The treatment will be given to her after fulfilling all the formalities as per the protocol. The subsequent follow-up will be on day 16 (visit 2), day 31 (visit 3), day 45 (visit 4), day 75 (visit 5), day 105 (visit 6), day 135 (visit 7), and completion of the active treatment (visit 8). Participants will visit the study site 8 times during the trial. The activity details during each visit are presented in Table 1 and Figure 1.

**Table 1 table1:** Study schedule.

Component	Screening	Baseline	Days 16 and 31	Day 45	Days 75 and 105	Day 135
Informed consent	✓					
Demographics and medical history		✓				
Assessment of Prakriti		✓				
Laboratory tests	✓			✓		
Clinical examination		✓	✓	✓	✓	✓
Assessment of Ayurvedic parameters		✓		✓	✓	✓
Concomitant medication		✓	✓	✓		
Rescue medication			✓	✓		
Assessment of adverse drug reactions			✓	✓		
Assessment of drug compliance			✓	✓		
Issue of trial drugs		✓	✓			
Control of Allergic Rhinitis and Asthma Test score	✓			✓		
Diagnostic nasal endoscopy		✓		✓		✓

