### Outcome Measures

#### Primary Outcome Measure

The primary outcome measure is the mean change in the Control of Allergic Rhinitis and Asthma Test (CARAT) score [21] at baseline and days 16, 31, 45, 75, 105, and 135. The CARAT questionnaire comprises 10 questions about upper and lower airway symptoms, sleep interference, activity limitation, and the need to increase medication over a 4-week period (Multimedia Appendix 1, also available on the web [22]). The total possible score ranges from 0 (minimum control) to 30 (maximum control) [21].

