### Ethical Considerations

This research protocol has been reviewed and approved by the Institutional Ethics Committee of Vardhman Mahavir Medical College, Safdarjung Hospital, New Delhi (IEC/VMMC/SJH/Project/2023-02/cc-320 dated 28.03.2023). Participants will receive an information sheet with the research details given in two languages (Hindi and English). Voluntary signed informed consent will be obtained from the participants before any clinical trial–related procedure. The participants will be informed by the investigator that all trial data recorded will be treated in strict confidence. During documentation and analysis of the trial, the individual participant will only be identified by their enrollment number.

Participant confidentiality will be guaranteed, and only researchers will have access to the data. Participants are nominally compensated for their loss of wages and conveyance charges by paying an amount of ₹100 (US $1.19) for every visit to the hospital during the study period. The safety of the trial intervention will be evaluated by recording the incidence of adverse events on every scheduled follow-up visit. All adverse events during the study timeline will be recorded and monitored per the International Council for Harmonisation of Technical Requirements for Pharmaceuticals for Human Use and Guideline for Good Clinical Practice guidelines. The investigator will report the same to the institutional ethics committee and the sponsors as soon as possible.

For facilitating appropriate reference standards for scientific, ethical, and safety issues before the trial begins, this protocol has been developed according to the 2013 SPIRIT (Standard Protocol Items: Recommendations for Interventional Trials) and CONSORT (Consolidated Standards of Reporting Trials) statements.

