### Strengths and Limitations

The strengths of this study include its randomized design and inclusion of enough participants to allow for adequate statistical power for subgroup analyses. This study uses the CARAT score and nasal endoscopy index, which are well-validated instruments to assess AR.

One potential limitation of this study is that the investigators were aware of the participants’ group assignment, and therefore, bias in favor of any particular group cannot be excluded. However, every effort was made to ensure blinding of the participants during the group allocation. An independent evaluator blind to study conditions was responsible for administering all study measures. A second limitation is the short intervention of the trial (ie, 45 days). However, the study follow-up was longer (ie, 90 days) to assess the recurrence of the symptoms/disease.

The results are expected to show better relief for AR for the treatment group. The protocol may also serve as a reference for the planning of similar clinical trials*.*

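### Table 1 stops adverse reaction assessment at day 45, against the text's rule of recording adverse events at every follow-up visit; its medication rows also stop there, although outcomes run to day 135

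*Protocol article*

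**What the plan says.** Study Procedure names Table 1 and Figure 1 as the place where the activities of each visit are set out. In Table 1, the row "Assessment of adverse drug reactions" is ticked for days 16 and 31 and for day 45, and is blank for days 75 and 105 and for day 135. The row "Rescue medication" has the same pattern. The row "Concomitant medication" has an additional tick at baseline and also ends at day 45.

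The text goes further. Ethical Considerations states: "The safety of the trial intervention will be evaluated by recording the incidence of adverse events on every scheduled follow-up visit". It adds: "All adverse events during the study timeline will be recorded and monitored". Study Procedure gives the dated follow-up visits as days 16, 31, 45, 75, 105 and 135.

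The sections Prior and Concomitant Medication and Rescue Medication both require the medicines used to be recorded, and neither sets an end date. The primary outcome, the CARAT score, is to be measured "at baseline and days 16, 31, 45, 75, 105, and 135". Strengths and Limitations gives the purpose of the period after treatment: "the study follow-up was longer (ie, 90 days) to assess the recurrence of the symptoms/disease".

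**The concern.** For adverse events, the table and the text give different instructions for the same three visits. Table 1 is the schedule that staff are likely to work from. If they follow it, adverse events that arise or come to light after day 45 have no scheduled point of capture, and the safety summary would fall short of what the text promises.

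For medication, the issue is how the late scores can be read. Trial treatment ends at day 45. A good CARAT score at day 75, 105 or 135 may reflect lasting benefit or another medicine taken since then. CARAT also asks about the need to increase medication over a 4-week period, so medication use enters the score directly. Without a record of that use in each arm, relapse covered by other treatment cannot be told apart from absence of relapse. The trial is open-label, so use after treatment could differ between the arms.

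**Working it through.** No sample size or power figure is involved. The check compares the table with the text and counts visits and days.

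**Step 1. What Table 1 schedules.**

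| Row | Screening | Baseline | Days 16, 31 | Day 45 | Days 75, 105 | Day 135 |
|---|---|---|---|---|---|---|
| Adverse drug reactions | – | – | yes | yes | – | – |
| Concomitant medication | – | yes | yes | yes | – | – |
| Rescue medication | – | – | yes | yes | – | – |
| CARAT score | yes | – | – | yes | – | – |
| Clinical examination | – | yes | yes | yes | yes | yes |
| Ayurvedic parameters | – | yes | – | yes | yes | yes |
| Nasal endoscopy | – | yes | – | yes | – | yes |

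The last three rows carry ticks after day 45. The late columns were therefore read correctly, and the blanks in the first four rows are not a fault of text extraction.

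**Step 2. The plan's own follow-up length.** Day 135 − day 45 = 90 days, which agrees with the figure in Strengths and Limitations.

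**Step 3. Size of the gap if Table 1 is followed.**
- Dated follow-up visits: 16, 31, 45, 75, 105, 135 = 6.
- Visits with adverse reaction assessment in Table 1: 16, 31, 45 = 3.
- Visits without it: 6 − 3 = 3, or 3 of 6.
- Days not covered: 90 / 135 = 0.67, or 67% of each participant's follow-up.

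**Step 4. Text against table, item by item.**
- *Adverse events:* the text fixes both the visits (each planned follow-up visit) and the period (the whole study). Table 1 omits three of those visits. This is a direct contradiction.
- *Concomitant and rescue medication:* the text requires recording but ties it to no visits. Table 1 is narrower than the text without breaking a stated visit rule.
- *CARAT:* the primary outcome section lists days 16, 31, 75, 105 and 135 in addition to baseline and day 45. Table 1 has only screening and day 45. This is a separate contradiction in the same table.

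**Step 5. Recall window of the late CARAT scores.** Four weeks is 28 days, and 75 − 28 = 47, which is later than day 45. From the day 75 visit onward, the whole recall period lies after the end of treatment, where Table 1 schedules no medication record.

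**The case against.** The strongest reply is that the text already provides for what the table lacks. Adverse events are promised for the whole study, and other and rescue medication must be recorded with no cut-off. Participants attend at days 75, 105 and 135 for clinical examination, so events could be noted then. This is a condensed article for a single site. The case report form is not shown and Figure 1 is not available, so it is not known that anything will be missed. All of this stands as a limit on the consequence. It does not remove the conflict between two statements in the same document.

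A second reply is that the terms differ: Table 1 speaks of adverse drug reactions, the text of adverse events. Assessing reactions during dosing and recording events throughout is a possible reading. The article does not say so, however, and no other row of Table 1 is dedicated to safety recording after day 45.

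A third reply concerns consistency. A site that follows Table 1 strictly would have no CARAT at days 75 to 135 to misread, and a site that follows the text would record events and medication as well. This is a fair limit on the medication argument. It bites if CARAT is collected as the primary outcome section requires while medication is recorded as Table 1 shows. It is also a reason to correct the CARAT row at the same time.

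A reader might infer that participants may use any rhinitis medicine once treatment ends. The document does not support that: Prior and Concomitant Medication asks them to consult the investigators first and gives no date on which this lapses. A reader might also want to state a bias in CARAT points at day 135. The document gives neither rates of use nor effects of other medicines, so any such figure would be invented.

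**Conclusion.** The point holds in two parts of unequal strength. For adverse events, Table 1 contradicts Ethical Considerations. On Table 1 alone, 3 of 6 dated follow-up visits and 90 of 135 days (67%) have no scheduled safety recording. For concomitant and rescue medication, Table 1 is narrower than the text, and the late CARAT results would be hard to interpret as evidence on recurrence.

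The counts describe Table 1, not the document as a whole. The practical loss depends on whether staff and the case report form follow the table, which cannot be seen from here. It would go too far to conclude that late safety data will certainly be missing, or that the day 75 to 135 comparison is biased by a known amount. The recurrence purpose is stated only in Strengths and Limitations; the primary outcome section lists the time points without giving that reason for them.

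**What to change.** Reconcile Table 1 and the case report form with Ethical Considerations, Prior and Concomitant Medication, and Rescue Medication:

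- Tick the adverse reaction, concomitant medication and rescue medication rows at days 75, 105 and 135.
- Use one term for the safety row, or state how adverse events and adverse drug reactions are each recorded.
- Reconcile the CARAT row of Table 1 with the time points in Primary Outcome Measure.
- In the report, show the number and proportion in each arm using other rhinitis medication after day 45, next to the CARAT results for days 75, 105 and 135.
- Recruitment began in September 2023, so some participants may already have passed these visits. State what was in fact recorded for them.

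The cost is a correction to the table and the form, and a few questions at visits already planned. The change concerns recording only, not which medicines may be used, and alters no sample size figure.

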**Figure 1 figure1:**
[figure not shown]
Study procedure. NLR: Naradiya Laxmivilas Rasa.

### Laboratory Tests

The laboratory tests (hematological/biochemical/ultrasound sonography) will be conducted at identified reputed laboratories or National Accreditation Board for Testing and Calibration Laboratories–accredited facilities. The laboratory tests and hematological examination carried out at baseline and the end of treatment (day 45) will collect the following values: hemoglobin (%), total leukocyte count, differential leukocyte count, erythrocyte sedimentation rate, absolute eosinophil count, fasting blood sugar, blood urea, serum creatinine, serum uric acid, total bilirubin, direct bilirubin, indirect bilirubin, serum alkaline phosphatase, aspartate aminotransferase, alanine aminotransferase, and total serum immunoglobulin E.

### Data Collection, Management, and Analysis

The data collection will include all information in the CRFs. All participants will be assigned an enrollment number, which will be used for CRFs and electronic databases. Consent forms and CRFs will be stored in locked cupboards, and electronic databases will be password protected. The data will be entered using the double-entry method for accuracy. All data will be accessible to the principal investigator and coinvestigators during and after the study, and will be available to sponsors and monitors as required. Data will be stored for 5 years and then destroyed. In case of dropout, 10% of the data will be inserted through the imputation technique. Proper documentation will be done to ensure accurate interpretation and verification related to the study. The analysis will be done by the CCRAS statistical unit. If any participants withdraw from the study prematurely, an attempt will be made to collect data for at least 1 month after enrollment, which includes the objective clinical and laboratory results. Data are important to the integrity of the final study analysis since early withdrawal could be related to the study drug’s safety profile.

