**Methods:**

This ongoing study is an open-label randomized controlled interventional trial, with a sample size of 90 both in the trial and standard control group (including dropouts, 20%), and will be carried out for 24 months. Participants in the trial group will receive Ayurvedic treatment, that is, Anu Taila Nasya (6 drops in each nostril for 7 days for 3 consecutive weeks), Naradiya Laxmivilas Rasa (250 mg twice per day), and Shirishadi Kwath (40 ml twice per day for 45 days). The participants in the control group will receive a fluticasone propionate nasal spray (2 sprays once per day for 45 days). The primary outcome will include the mean change in the Control of Allergic Rhinitis and Asthma Test score, and the secondary outcomes will include the mean change in the nasal endoscopy index (assessment of nasal membrane color, pale or hyperemia; rhinorrhea, watery or yellow; and inferior turbinate swelling, hypertrophy) and the mean change in the laboratory tests.

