### Statistical Methods

Continuous variables will be presented as means, SDs, medians, and ranges. Categorical variables will be summarized with frequencies and percentages. When inferential analyses are conducted for continuous variables, they will be tested for normality. Nonparametric methods will be used for comparison of nonnormal data. Within-group comparisons will be done by using paired *t* tests, while between-group comparisons will be done using independent sample *t* tests for the data with normal distribution. Nonnormal data within the group will be compared using the Wilcoxon sign rank test, while between-group comparisons will be done by using the Mann-Whitney *U* test. Categorical data between groups will be compared using the *χ*^2^ or Fisher exact test. A 2-sided *P* value <.05 will be considered statistically significant. Per-protocol and intention-to-treat analyses will be carried out at the end of the study. All data will be analyzed using STATA 16.1 (StataCorp).

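### The protocol presets imputation after dropout at 10% of the data, which is undefined, not reconciled with the planned 20% dropout, and leaves the intention-to-treat set open to choice

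*Protocol article*

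**What the plan says.** Data Collection, Management, and Analysis contains the only missing-data rule in the article: "In case of dropout, 10% of the data will be inserted through the imputation technique". The unit of the 10% (participants, values, or the dropouts' own data) is not given, nor is the choice of which missing values are filled.

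Sample Size plans for twice that percentage of dropout: "Assuming a dropout rate of 20%, a total of 90 participants, 45 per group, will be included in this trial". The abstract repeats the 20% figure in its Methods paragraph.

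Statistical Methods promises both per-protocol and intention-to-treat analyses. It compares arms by independent-samples t test, or Mann-Whitney if the data are not normal, with this threshold: "A 2-sided *P* value <.05 will be considered statistically significant". Randomization and Allocation keeps the schedule with the biostatistician/data analyst, and the abstract describes the trial as open-label.

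**The concern.** A missing-data rule should say how missing values are handled, however many there turn out to be. This one fixes the quantity in advance. If more is missing than the quota covers, someone must decide which participants are filled in and which are dropped. The analysed set is then neither all randomised participants nor the complete cases, and the document does not say who belongs to it.

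The discretion matters here. Treatment is open-label, and the randomization schedule rests with the function that handles the data. The same section that sets the quota also acknowledges that early withdrawal may be linked to the safety of the study drug. If dropout is informative, the choice of whom to impute can move the treatment comparison.

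A second, conditional issue is precision. If single imputed values enter the t test as though they had been observed, the sample size grows without new information, and under some techniques the standard error is then too small.

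**Working it through.** **Inputs.** Sample Size: 45 per arm, 90 in total, 20% dropout, SD 6, difference 14 - 10 = 4, 80% power. Statistical Methods: two-sided 5%. Data Collection, Management, and Analysis: the 10% quota. Outcome Measures: CARAT at baseline and six follow-up days, seven assessments in all.

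**1. The plan's own figure.** n = 2 × 6² × (1.96 + 0.84)² / 4² = 35.28 per arm. The article states 35; rounding up gives 36. Dropout: 35/0.8 = 43.75, so 44; 36/0.8 = 45. The stated 45 per arm is reproduced, and the imputation rule does not affect it.

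**2. Quota as a share of participants.** Expected dropouts: 0.20 × 90 = 18, or 9 per arm. Quota: 0.10 × 90 = 9, or 4-5 per arm. Left out: 18 - 9 = 9, with no rule for selecting them.

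**3. Quota as a share of all CARAT values.** Assume the 20% leave evenly over the six follow-up visits. They then miss 6, 5, 4, 3, 2 or 1 of seven assessments, on average 3.5. Missing values overall: 0.20 × 3.5/7 = 10%, which equals the quota. At the last visit, however, all 20% are missing.

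**4. Quota as a share of the dropouts' data.** 0.10 × 9 = 0.9, about one participant per arm. Nearly all dropouts would be excluded.

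**5. Type I error if imputed values are treated as observed.** Take n observed and i imputed per arm, N = n + i, no true difference, and dropout completely at random and equal between arms. Filling in each arm's own mean leaves the difference in means and the sums of squares unchanged, so reported SE / true SE = √[n(n-1) / (N(N-1))]. The type I error is the two-sided tail beyond (5% critical t on 2N - 2 df) × this ratio, on 2n - 2 df.

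| n observed | i imputed | SE ratio | Type I error |
|---|---|---|---|
| 36 | 1 | √(1260/1332) = 0.97 | 5.7% |
| 36 | 4 | √(1260/1560) = 0.90 | 7.8% |
| 36 | 5 | √(1260/1640) = 0.88 | 8.6% |
| 36 | 9 | √(1260/1980) = 0.80 | 11.7% |
| 41 | 4 | √(1640/1980) = 0.91 | 7.4% |
| 40 | 5 | √(1560/1980) = 0.89 | 8.2% |

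Simulations of 40,000 null trials agree with these values (for example 7.7%, 8.6% and 11.8% for 4, 5 and 9 imputed with 36 observed). Complete-case analysis of 36 per arm gives about 5%.

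**6. Other single imputations, same number of trials.** Filling in the mean of both arms pooled gives 4.8-5.1%. Setting the change to zero gives about 5% when the numbers dropping out vary at random, and less when they are fixed equal. Carrying the last value forward (assumed correlation 0.6 and earlier mean change 7) gives 4.6-4.8%. These methods can bias the estimated effect, but they do not inflate type I error in this setting.

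**The case against.** Three objections carry weight.

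First, the percentages may have different denominators: 20% is of participants, 10% is of data. Step 3 shows that they can coincide. A reader might infer a flat arithmetical contradiction, and the document does not support that. What remains is that the two figures are not reconciled and that the agreement disappears at the last visit.

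Second, no technique is named. A condensed article may leave the imputation model and its variance handling to a statistical analysis plan, so their absence is no finding. A reader might infer from the idea of inserting data that single values will be treated as observed and that the false-positive rate will therefore exceed 5%. The text does not say this, and step 6 shows that it is not true of single imputation in general. Nor does the figure of about 12% describe the quota read as a share of participants: it requires all 9 dropouts per arm to be imputed.

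Third, a mixed model cannot simply be prescribed. Outcome Measures lists CARAT at six follow-up days, but Table 1 marks it only at screening and day 45. Under Table 1 there is one post-baseline value and nothing repeated to model.

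None of this rescues the quota. A later plan can supply a technique, but it cannot impute whatever is missing and also hold to a preset 10%.

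**Conclusion.** The point holds as a badly fixed rule. The protocol presets the amount of imputation without defining its unit or whose values are filled, and it does not connect the 10% to its planned 20% dropout. The size depends on the reading: about 9 of 18 expected dropouts left out if participants are meant, about 8 of 9 per arm left out if the dropouts' own data are meant, and up to 20% missing at the final assessment against a 10% overall share if visit values are meant. Under the first two readings the intention-to-treat set is open to choice by someone who may know allocation; under the third, nothing says how the last visit is completed. The article does not state that the holder of the schedule will personally run the analysis, which it assigns to the sponsor's statistical unit. It does, however, give the schedule to the data analyst role and describes no separation.

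Inflated type I error is a conditional risk, not a stated error. It is about 7-8% (up to 8.6% with 36 observed per arm) if 4-5 values per arm are filled with the arm's own mean and treated as observed, and about 5% or less under the other single imputations checked. These figures assume dropout completely at random, equal between arms, and no covariates. The sample size is unaffected.

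**What to change.** Delete the 10% quota. State that the intention-to-treat analysis includes every randomised participant in the assigned arm, and name the primary time point for CARAT. Then prespecify one of two methods:

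- Multiple imputation of every missing CARAT value at that time point, done separately by arm, with the difference in mean change combined by Rubin's rules. This works under either CARAT schedule. Rubin's rules combine an estimate and its standard error, so the pooled mean difference would be the intention-to-treat result rather than a Mann-Whitney P value.
- If CARAT is in fact collected at all the days in Outcome Measures, a mixed model for repeated measures on all observed values. Outcome Measures and Table 1 must be reconciled before this option is chosen.

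The cost is wording and a little programming, with no change to recruitment, visits or sample size. Confidence intervals become slightly wider because they reflect the information actually collected. With 36 observed per arm and no help from other variables, the standard error is about 6 × √(2/36) = 1.41, against 6 × √(2/45) = 1.26 if imputed values counted as real ones. The change should be in place before the analysis, which the Results section expects to be complete by February 2025.

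### The minimum data collection after withdrawal ends about 15 days before the day 45 assessments and does not name CARAT, so intention-to-treat outcomes for early leavers are not assured

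*Protocol article*

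**What the plan says.** The rule is in the protocol article, Data Collection, Management, and Analysis. After premature withdrawal, "an attempt will be made to collect data for at least 1 month after enrollment, which includes the objective clinical and laboratory results". The section gives its reason: "Data are important to the integrity of the final study analysis since early withdrawal could be related to the study drug’s safety profile". It also says "In case of dropout, 10% of the data will be inserted through the imputation technique", without naming a method.

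Under Primary Outcome Measure, "The primary outcome measure is the mean change in the Control of Allergic Rhinitis and Asthma Test (CARAT) score", assessed "at baseline and days 16, 31, 45, 75, 105, and 135". The CARAT row of Table 1 (Study Procedure), as it reads in the text available, is ticked only at screening and day 45. The laboratory panel is planned before treatment and at day 45, the end of treatment (Laboratory Tests; Table 1). Endoscopy is an outcome at baseline and day 45 (Secondary Outcome Measures), and Table 1 adds day 135.

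Statistical Methods promises that "Per-protocol and intention-to-treat analyses will be carried out at the end of the study". Sample Size allows for 20% dropout in a total of 90.

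**The concern.** An intention-to-treat comparison needs outcomes on everyone randomized, including those who leave. Here the clock for the minimum runs from enrollment, not from the withdrawal, and it expires before the end of treatment. Following the rule to the letter need not produce a single day 45 value. The laboratory results that it asks for have no scheduled post-baseline draw inside the minimum period. A participant who leaves on day 35, perhaps because of a suspected reaction, has already passed the minimum, so nothing more is required, although safety is part of the rule's stated reason.

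The trial is open-label and compares a three-product regimen with a once-daily spray. Departures that are unequal between arms and related to outcome are plausible. If those outcomes are not collected, the comparison becomes one of completers or of imputed values, and the difference cannot be repaired at analysis.

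**Working it through.** **Step 1. The plan's own figures.** Sample Size uses SD 6, a difference of 14 − 10 = 4, and 1.96 + 0.84 = 2.80:

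n = 2 × 6² × 2.80² ÷ 4² = 564.48 ÷ 16 = 35.28, stated as 35 per group.

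For 20% dropout, 35 ÷ 0.8 = 43.75, so 44; an unrounded-down 36 ÷ 0.8 = 45. The stated 45 per group, 90 in total, is reproduced and is not in dispute. Planned dropout is 0.20 × 90 = 18, or 9 per group.

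**Step 2. The minimum against the visit days.** One month is taken as 30 days.

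| Assessment | Scheduled after baseline | Clearly inside day 30? |
|---|---|---|
| Laboratory tests | 45 | none |
| Endoscopy | 45 (Table 1 also 135) | none |
| CARAT, by Table 1 | 45 | none |
| CARAT, by Primary Outcome Measure | 16, 31, 45, 75, 105, 135 | day 16 only; day 31 at the edge |

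The minimum ends 45 − 30 = 15 days before day 45 and 135 − 30 = 105 days before the last visit.

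**Step 3. How many participants.** The timing of dropout is not given, so two assumptions mark a range.
- All 18 leave within 45 days: day 45 values are not assured for any of the 18. If departures are even, 18 × 30/45 = 12 leave by day 30 and 6 leave between days 30 and 45, after the minimum has expired.
- Departures spread evenly over 135 days: 18 × 45/135 = 6 leave before day 45 (4 by day 30, 2 between days 30 and 45). The other 12 leave after their day 45 visit was already due.

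**Step 4. The fallback.** If the 10% to be imputed means participants (an assumption), it covers 0.10 × 90 = 9, half of the planned 18.

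**Step 5. Possible bias.** With a fraction m missing in each arm,

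all-randomized difference = (1 − m) × D_completers + m × D_dropouts = D_completers + m × (D_dropouts − D_completers).

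| Gap among dropouts differs from completers' gap by | Shift, m = 0.20 (18 of 90) | Shift, m = 0.067 (6 of 90) |
|---|---|---|
| 1 point | 0.2 | 0.07 |
| 2 points | 0.4 | 0.13 |
| 4 points | 0.8 | 0.27 |

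These compare with a planned difference of 4 points.

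**Step 6. Power.** At a difference of 4 and SD 6, power is 88.5% with outcomes on 45 per group and 80.7% on 36 per group. The planned loss is already paid for in power. What remains is bias, which a larger sample does not remove.

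**The case against.** The strongest reply is that the rule sets a minimum and a partial list. It says at least a month, so nothing stops collection at day 45 or later, and it says that the data include objective and laboratory results, which does not exclude CARAT. A reader might infer that collection stops at day 30 and covers only objective measures; the wording does not support that. This stands. It does not supply a requirement, and what is left to discretion is likely to be done unevenly.

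A reader might also infer that dropouts would have no outcome at all. That goes too far. The section provides for imputation, however vaguely, and under Primary Outcome Measure someone who leaves after day 16 or day 31 may already have a post-baseline CARAT. The conflict between that list and Table 1 is a separate matter.

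The request for laboratory results can be read as asking for an unscheduled draw at withdrawal. That is possible, but the text ties no draw to the withdrawal.

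One could also try to shorten the window further. Study Procedure uses the word enrolled loosely, so a month counted from consent, up to a week before baseline, would end near treatment day 23 (30 − 7). But the same section says that "the participant will be enrolled in the study, with this day being recorded as visit 1 or the baseline visit", so day 30 is the fair reading.

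Finally, participants may leave at any time, so data can only be requested; the article condenses a fuller protocol; and 72 participants were enrolled by May 2024. The first limits what any rule can achieve. The second does not excuse a rule that the article does state and fixes too short. The third limits the benefit of a change to those not yet through follow-up.

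**Conclusion.** The point holds in a limited form, as an inexpensive improvement and not as a fatal flaw. The required minimum ends about 15 days short of day 45 and leaves out the primary outcome by name. Day 45 values are therefore unassured for between about 6 and 18 of the 18 expected dropouts, depending on when they leave. The illustrative shift in the treatment difference is 0.2 to 0.8 points with 20% missing per arm, and smaller if fewer leave before day 45. It rests on assumed gaps among dropouts and equal missingness in both arms, neither of which the documents give.

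Two stronger figures are tempting and are not supported. One is that day 45 data are required for none of the 18; that is so only if every dropout occurs before day 45. The other is a collapse of the difference from 4.0 to 0.8 points. It follows from 0.7 × 14 − 0.9 × 10 = 0.8, which needs 30% against 10% dropout and no improvement at all in anyone who leaves. The documents support neither input, so it is a chosen extreme and not an estimate.

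**What to change.** Replace the minimum of one month from enrollment with the following.

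1. Participants who stop trial medication or attend less, but do not withdraw consent for data collection, stay on the existing visit schedule at least through day 45 and preferably to day 135.
2. The rule names CARAT, together with the day 45 laboratory tests and endoscopy.
3. If a visit is declined, CARAT may be taken by telephone.
4. The case report form records stopping treatment separately from leaving the study.

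The CARAT visit days in Primary Outcome Measure and Table 1 should be reconciled at the same time, so that the rule points to one schedule.

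The change needs no new procedure or staff: project staff already telephone participants, the laboratory panel and endoscopy are in the plan, and visits carry the existing ₹100 payment. The cost is a few more visits or calls to people who have stopped treatment, and an amendment, possibly with ethics review, while the trial is under way. It would help only participants still to be enrolled or still in follow-up. The sample size does not change.
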